## Abstract

**Background:**

The prevalence of type 2 diabetes is rising with the majority of patients practicing inadequate disease self-management. Depression, anxiety, and diabetes-specific distress present motivational challenges to adequate self-care. Health systems globally struggle to deliver routine services that are accessible to the entire population, in particular in rural areas. Web-based diabetes self-management interventions can provide frequent, accessible support regardless of time and location

**Objective:**

This paper describes the protocol of an Australian national randomized controlled trial (RCT) of the OnTrack Diabetes program, an automated, interactive, self-guided Web program aimed to improve glycemic control, diabetes self-care, and dysphoria symptoms in type 2 diabetes patients.

**Methods:**

A small pilot trial is conducted that primarily tests program functionality, efficacy, and user acceptability and satisfaction. This is followed by the main RCT, which compares 3 treatments: (1) delayed program access: usual diabetes care for 3 months postbaseline followed by access to the full OnTrack Diabetes program; (2) immediate program: full access to the self-guided program from baseline onward; and (3) immediate program plus therapist support via Functional Imagery Training (FIT). Measures are administered at baseline and at 3, 6, and 12 months postbaseline. Primary outcomes are diabetes self-care behaviors (physical activity participation, diet, medication adherence, and blood glucose monitoring), glycated hemoglobin A1c (HbA1c) level, and diabetes-specific distress. Secondary outcomes are depression, anxiety, self-efficacy and adherence, and quality of life. Exposure data in terms of program uptake, use, time on each page, and program completion, as well as implementation feasibility will be conducted.

**Results:**

This trial is currently underway with funding support from the Wesley Research Institute in Brisbane, Australia.

**Conclusions:**

This is the first known trial of an automated, self-guided, Web-based support program that uses a holistic approach in targeting both type 2 diabetes self-management and dysphoria. Findings will inform the feasibility of implementing such a program on an ongoing basis, including in rural and regional locations.

**Trial Registration:**

Australian and New Zealand Clinical Trials Registration number: ACTRN12612000620820; https://anzctr.org.au/Trial/Registration/TrialReview.aspx?ACTRN=12612000620820 (Archived by WebCite at http://www.webcitation.org/6a3BeXC5m).

## Introduction

Diabetes mellitus affects an estimated 346 million people globally and type 2 diabetes accounts for 85% to 90% of all cases [1]. In Australia, type 2 diabetes affects 4% of the population [2]. Diabetes constitutes the eighth-highest burden of disease in Australia and type 2 diabetes accounts for 92% of this burden [3]. With the rapidly rising prevalence of diabetes, the effects of inadequate diabetes self-management continue to increase and resulting diabetes complications and premature mortality become more urgent to address. Diabetes is the leading cause of blindness, end-stage renal disease, and lower limb amputation in the world [1]. Moreover, the effects of diabetes on quality of life, mental health, work productivity, and other intangible losses are substantial and add further to the diabetes-related burden to society.

Depression [4,5] and anxiety [6] are significantly more prevalent in people with diabetes than in the general population. Comorbid mental health conditions are barriers to effective diabetes self-care [7] and further increase diabetes-related expenditures [8]. Dysphoria complicates the achievement of adequate glycemic control through multiple pathways. Comorbid depression and/or anxiety with diabetes predisposes individuals to diabetes-specific distress [9,10] and affects glycemic control [11] both directly (via physiological mechanisms [8-10]) and indirectly by reducing motivation for adequate self-management [12-14]. Even subclinical manifestations, such as dysphoria, are associated with clinically deleterious outcomes, including reduced self-care [7], poorer glycemic control [15,16], increased incidence and progression of diabetes complications [17,18], and greater disability [19]. Stress contributes to other common physical comorbidities in diabetes patients, including metabolic syndrome and cardiovascular disease [20]. Diabetes-specific distress (DSD)—the emotional and psychological burden posed by diabetes [21]—accounts for a high proportion of variance in depression [22] and further impedes self-management [23]. Combined effects of inadequate glycemic control and dysphoric mood in diabetes [21,22] thus call for urgent intervention.

Prior research indicates the need for behavioral diabetes self-management interventions to incorporate psychological and emotional support components for optimum efficacy [23]. Improvements in diabetes self-care are strongly associated with improved glycemic control [24,25], so behavioral interventions to support diabetes self-care might also improve clinical outcomes [26]. However, improvements in glycemic control do not generally result in significant improvements in mood [23], nor do psychological treatments for depression and anxiety in people with diabetes reliably produce improvements in glycemic control [27]. Despite the limited impact of single-focused interventions in diabetes [28], self-management interventions typically fail to address both issues. Furthermore, trials on self-management interventions often only follow-up participants for relatively short periods (eg, ≤6 months [29]) so that long-term effects remain undetermined.

There are many barriers to adequate treatment of type 2 diabetes within health systems, including a shortage of health professionals, inadequate availability of services, limited access in rural and remote regions, practitioner/patient communication problems, time pressures in medical consultations, and limitations in the skills and confidence of health professionals in the provision of psychological interventions [30]. Patients often struggle to manage the complexity of type 2 diabetes treatment regimens [31], to recognize dysphoria symptoms [32,33], acknowledge their need for support, and find the motivation to overcome barriers to a healthy lifestyle [34]. Shortcomings in health care services particularly affect patients at risk of psychological comorbidities and the number of these patients will escalate sharply as the incidence of diabetes increases [4].

Recent evidence demonstrates that Web-based diabetes self-management interventions have potential efficacy, feasibility, user acceptability, and uptake [29]. Web programs have demonstrated significant improvements in clinical, behavioral [35-37], psychological, emotional, and psychosocial outcomes [38], as well as a strong uptake and acceptability by both mature [39] and novice users [40].

Recently trialed Web-based diabetes self-management programs based on social cognitive theory (SCT) [41] have demonstrated efficacy [35,42,43]. Central tenets of SCT include self-efficacy, or one’s belief in their capabilities to execute desired courses of action, and outcome expectancies, or personal predictions of likely outcomes resulting from certain courses of action [41]. SCT encompasses the key recommendations in national practice guidelines for diabetes management [44]. These include encouraging patient empowerment (promoting self-efficacy), ongoing monitoring of target outcomes (self-evaluation), and providing diabetes education (instructions). Therefore, SCT provides a theoretical avenue by which to address both behavioral self-management and emotional issues [45]. Self-efficacy has significant positive associations with behavioral outcomes including physical activity participation [46,47], nutrition intake [48,49], weight loss [50], and diabetes self-care [51], as well as with emotional outcomes, including depressive symptoms [52], in people with diabetes.

Despite the growth in supportive evidence on Web-based diabetes programs for self-management, there are some inconsistencies in their results and further data are needed on their potential to improve glycemic control [53]. Lorig et al [54] trialed a diabetes self-management intervention that included modules to assist users in coping with emotional challenges both related and unrelated to diabetes. Although improvements were found in self-efficacy, patient activation, and glycated hemoglobin (HbA_1c_) at 6 months postenrollment, there were no significant improvements in health behaviors, including exercise participation. Emotional outcomes and effects on long-term glycemia were not determined. On the other hand, Glasgow and colleagues [36] reported that their Internet-based diabetes education program (D-Net) did not significantly improve mood or glycemic control, but produced significant improvements in behavioral and psychosocial outcomes. Although current trials show that Web-based diabetes programs have substantial promise, there remains a need to enrich available data on their effects on both mood and glycemia. Given the close mutual influences between dysphoria and diabetes self-management, including the challenging context of psychosocial [55] and emotional stressors [56] in which self-management is attempted, a Web intervention that utilizes a holistic approach to diabetes self-management is required. Such a program would allow users to address both the behavioral and emotional challenges of diabetes in context.

Developing and maintaining commitment to any significant behavior change is challenging. Over the last 30 years, motivational interviewing [57] has demonstrated an ability to enhance motivation, particularly in addictive disorders (where it began), but also in some other behavioral domains [58]. However, until now, its effects on behavior change and glycemic control in diabetes have been inconsistent with only a minority of trials having significant differential effects [59]. Recently, a new approach to eliciting motivation, which uses a motivational interviewing style but trains participants to use motivational imagery in their everyday life, has been advanced [60]. This approach, Functional Imagery Training (FIT), applies 10 years of theoretical and empirical work on the nature and modulation of desires [61]. Personalized multisensory imagery about the benefits of health maintenance behaviors, past successes, and effective strategies is elicited. This is described as television advertisements in which the participant is the actor and is reliving an event or imagining a future event. Participants are asked to practice this imagery when they undertake a routine everyday task and to set electronic reminders for times when they need to undertake a health routine or avoid a dysfunctional behavior. Imagery is cued using photos taken by the participant and is refreshed using new events that illustrate actual gains and effective strategies. Commitment and social support for the goal is elicited by sharing a brief recorded statement about the goal, why it was adopted, how it will be done, and why it will be successful; this recording is replayed if motivation is fading. Brief phone calls by the therapist remind the participant to practice their imagery and help them solve problems by using it.

The study described subsequently comprises a randomized controlled trial (RCT) involving the OnTrack Diabetes program, an automated Web-based intervention aimed to achieve and maintain improvements in type 2 diabetes self-management and dysphoria symptoms. It compares delayed and immediate access to the program, and immediate access supplemented by FIT-based coaching.

## Methods

### The OnTrack Diabetes Program

The development of OnTrack Diabetes is described in a companion paper [62](see Figure 1 for screenshot). The program targets physical activity participation, nutrition, adherence to health routines, and mood disturbance (depression, anxiety, and diabetes-related everyday stressors). Specifically, the program includes informational resources: goal setting, planning, and creating routines for self-care behaviors; feeling confident and problem solving via interactive tools; goal attainment scaling via self-monitoring tools, quizzes, and automated feedback graphs; relaxation and mindfulness audios; and an electronic diary. Access to health care providers is also promoted by encouraging users to establish a diabetes care team. Further, the program addresses the independent effects of depression, anxiety, and diabetes-specific distress by enabling users to provide personalized responses in the emotional support tools regarding both diabetes-specific and nonspecific emotional challenges. Although program sections appear in an ordered structure, users can choose to undertake segments in any order—a feature intended to foster user empowerment [63]. Both provided and entered text is minimized with extensive use of icons and pictures and simple sentences and vocabulary so that reading requirements do not exceed Year 7 educational levels.

**Figure 1 figure1:**
[figure not shown]
Screenshot of the OnTrack Diabetes home page.

### Design and Setting

A pilot trial of the program is initially implemented to test for program functionality and to provide an indication of program efficacy, user acceptability, and satisfaction. Following the pilot, a RCT with the participant as the unit of randomization is implemented. The trial is conducted Australia-wide and access is ongoing. The research team is based at the Mitsubishi Centre for Rural and Remote Health at the Wesley Research Institute in Brisbane.

The RCT evaluates the efficacy of the OnTrack Diabetes program in improving the primary outcomes glycemic control (HbA_1c_ level) and diabetes-specific distress symptoms, and the secondary outcomes of depression, anxiety, physical activity participation, diet, blood glucose self-monitoring, and medication taking. User acceptability, ease of use, utility, program satisfaction, and implementation feasibility are also assessed.

It is hypothesized that at 3 months postbaseline, the immediate access plus FIT condition will show the greatest improvements in primary and secondary outcomes compared with the immediate access and the delayed access conditions. Results of the immediate access and the delayed access conditions are expected to be similar at 6 months when both conditions will have received the full intervention. A CONSORT flow diagram for the trial is shown in Figure 2.

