### Measures

Primary outcomes include diabetes self-care behaviors, HbA_1c_ level, and diabetes-specific distress. Secondary outcomes include depression, anxiety, (medication taking, nutrition intake, physical activity, and blood glucose self-monitoring), quality of life, and user evaluations of the program. Measures are administered at baseline and the 3-, 6-, and 12-month follow-up time points. Table 1 in Multimedia Appendix 1 lists the measures.

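### Diabetes self-care behaviors are primary outcomes in the Abstract and the first sentence of Measures but secondary in Design and Setting, so it is unsettled whether a self-care effect is a primary result

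*Protocol article*

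**What the plan says.** Three sections of the protocol article assign outcomes to classes.

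- **Abstract, Methods.** Self-care is primary and its four components are named: "Primary outcomes are diabetes self-care behaviors (physical activity participation, diet, medication adherence, and blood glucose monitoring". HbA1c and diabetes-specific distress complete the primary list. The secondary list reads "Secondary outcomes are depression, anxiety, self-efficacy and adherence, and quality of life".
- **Design and Setting.** The primary list has two members: "the primary outcomes glycemic control (HbA_1c_ level) and diabetes-specific distress symptoms". The same four behaviors are placed in the other class, among "the secondary outcomes of depression, anxiety, physical activity participation, diet, blood glucose self-monitoring, and medication taking".
- **Measures, first sentence.** Self-care is primary again: "Primary outcomes include diabetes self-care behaviors, HbA_1c_ level, and diabetes-specific distress".
- **Measures, second sentence.** The four behaviors then appear, in parentheses with no label in front, inside the secondary list: "Secondary outcomes include depression, anxiety, (medication taking, nutrition intake, physical activity, and blood glucose self-monitoring), quality of life".

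The hypothesis in Design and Setting is framed by these labels. It expects that "the immediate access plus FIT condition will show the greatest improvements in primary and secondary outcomes" at 3 months. Nothing in the article reconciles the lists.

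**The concern.** The label decides how a self-care effect is read. Suppose one or more behaviors improve while HbA1c and distress do not. Under the Abstract, the trial has a positive primary result. Under Design and Setting, it has missed both primary outcomes and has a secondary finding. The data are the same and the conclusions differ.

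That pattern is realistic on the article's own evidence. The Introduction describes one earlier web program that improved HbA1c without improving health behaviors. It describes another, an Internet-based education program, that improved behavioral outcomes without improving glycemic control. The Results section says the trial is already running. Unless the class of self-care is fixed and dated now, it could be settled after the results are known.

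**Working it through.** **1. The statements side by side**

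| Place | HbA1c | Distress | Four self-care behaviors |
|---|---|---|---|
| Abstract, Methods | primary | primary | primary |
| Design and Setting | primary | primary | secondary |
| Measures, first sentence | primary | primary | primary (as a group) |
| Measures, second sentence | not listed | not listed | apparently secondary |

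The first two columns are consistent. The conflict is confined to the last. It does not depend on the ambiguous parenthesis in Measures: without that row, Design and Setting still conflicts with the Abstract and with the first sentence of Measures.

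**2. How many primary outcomes each reading gives**

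- Design and Setting: HbA1c + distress = 2.
- Abstract or Measures, self-care as one outcome: 2 + 1 = 3.
- Abstract or Measures, four behaviors counted separately: 2 + 4 = 6.

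The text does not say whether 3 or 6 is meant.

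**3. The plan's own sample size figure**

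Sample Size and Retention gives N = 210 and a detectable f² = .046. It does not state alpha, power or the number of tested predictors. Assume alpha 0.05, 80% power and two treatment contrasts tested jointly (three arms), with one baseline covariate. The test is a noncentral F with 2 numerator df, 210 − 3 − 1 = 206 denominator df, and noncentrality 0.046 × 210 = 9.66. Power is 79.5%. The f² detectable at 80% power is .0466, and the N needed for f² = .046 is 213. The stated figure therefore reproduces to within rounding. It is not in error, but under these assumptions it corresponds to a single outcome tested at an unadjusted 5%, so it does not reveal which primary set was intended.

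**4. What the choice of set changes (illustration)**

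Assume independent tests at an uncorrected 5%, one contrast, one time point, and any one significant primary outcome counted as a primary finding. The chance of at least one false positive among m primary outcomes is 1 − 0.95^m:

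- m = 2: 1 − 0.95² = 0.0975, or 9.8%
- m = 3: 1 − 0.95³ = 0.1426, or 14.3%
- m = 6: 1 − 0.95⁶ = 0.2649, or 26.5%

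Correlation among outcomes lowers these. For m = 6 the figure is about 25% at a common correlation of 0.2 and about 21% at 0.5. Both correlations are assumptions.

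The set also matters if alpha were split equally. With the step 3 test at 0.05/m, N = 210 and f² = .046, power per outcome would be 70.6% (m = 2), 65.1% (m = 3) or 55.7% (m = 6). The N for 80% power would be 254, 278 or 317. The article does not say that such a split is planned.

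**The case against.** Several counter-arguments have weight.

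- **An article condenses a fuller protocol.** This excuses omissions. It does not excuse statements that cannot all be true, and no unseen analysis plan or measures table can make the Abstract and Design and Setting agree.
- **The parenthesis in Measures may be an editing slip.** This stands. With no noun in front, it could be a displaced gloss on self-care from the sentence before, where the Abstract has a similar one. It is weak evidence of a further classification, and the point does not rest on it.
- **The error rates measure multiplicity, not the contradiction.** This also stands. They assume no correction and an any-one-significant rule, neither of which the article states. Multiplicity handling may be in an analysis plan that is not shown, so its absence is not part of this point.
- **The secondary lists differ too.** Self-efficacy appears only in the Abstract's list, and quality of life is absent from Design and Setting. This is minor: Measures does not claim to be exhaustive, and its table is not shown.

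A reader might also infer three stronger things that the documents do not support.

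- That the trial's success cannot be judged at all. HbA1c and distress are primary in every primary list, so results on those two can be judged.
- That the choice is simply between 2 and 6 primary outcomes. Self-care as one outcome, giving 3, is an equally natural reading.
- That Design and Setting is the correct list and self-care should be demoted. The Abstract's Objective puts self-care among the program's aims, and two of the statements make it primary. Nothing shown says which list was prespecified.

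**Conclusion.** The contradiction is real and rests on the text alone. Self-care is primary in the Abstract and in the first sentence of Measures, secondary in Design and Setting, and apparently secondary in the second sentence of Measures. The defect is limited to the status of self-care. It matters because a behavior-only result would be classed differently depending on the section followed.

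The primary set has 2, 3 or 6 members. Under the assumptions in step 4, that moves the chance of at least one false-positive primary result from 9.8% to 14.3% or 26.5%. Those figures show scale only. The sample size figure is not faulted. The point should be resolved before outcome data by arm are examined.

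**What to change.** Before any outcome data by arm are examined:

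1. Establish which primary set was prespecified, by checking the trial registration and the ethics-approved protocol. Neither was available for this review.
2. Make the Abstract, Design and Setting, and Measures all state that set.
3. Say explicitly whether self-care is primary or secondary. If it is primary, say whether it is one outcome or four.
4. Remove self-care from the other list, and clear up the parenthesis in the second sentence of Measures.
5. Date the decision and record that it was made without sight of outcome data by arm.

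If the registration and approved protocol agree, the cost is a wording correction and a registry check, with no new data. If they disagree, or if the sponsor wishes to depart from what was prespecified, this becomes a change of primary outcome in a trial already underway. It should then be handled as a dated, reasoned amendment.

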### Statistical Analyses

Preliminary analyses assess for baseline differences and subsequent analyses control for any observed differences. The primary analyses will comprise multiple regressions, predicting posttreatment and follow-up results from baseline measures and treatment contrasts with multiple imputation being used to predict missing data. Mixed-model ANOVAs with repeated measures will also be applied to confirm whether effects are still obtained without imputations. Both methods allow an intention-to-treat approach to the data. Repeated measures ANOVAs will be used to evaluate differences in change scores between the study time points among the 3 study conditions.

User satisfaction, perceived ease of use, and usefulness are examined with ANOVAs and program reach, acceptability, implementation feasibility, and outreach are assessed using the Reach Effectiveness Adoption Implementation Maintenance (RE-AIM) framework [64]. This will be operationalized using the OnTrack Diabetes Evaluation Questionnaire, which asks about users’ perceptions of the program’s acceptability, issues with feasibility, and outreach (ie, ability to access the program and barriers to access including poor broadband network availability). The inclusion of residents of rural and regional areas enriches this evaluation as will quantitative data about participants’ exposure to the program.

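### The primary outcomes are several, unordered and listed inconsistently, and the stated detectable effect fits one outcome at a time, so the type I error of a primary claim is undefined and probably above 5%

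*Protocol article*

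**What the plan says.** Three places in the protocol article define the primary set, and they differ.

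- Design and Setting speaks of "improving the primary outcomes glycemic control (HbA_1c_ level) and diabetes-specific distress symptoms, and the secondary outcomes of depression, anxiety, physical activity participation" and then places diet, glucose self-monitoring and medication taking with the secondary outcomes. That makes two primary outcomes.
- The Abstract (Methods) says: "Primary outcomes are diabetes self-care behaviors (physical activity participation, diet, medication adherence, and blood glucose monitoring), glycated hemoglobin A1c (HbA1c) level, and diabetes-specific distress". That is three domains, or six measures if the four behaviors are counted separately.
- Measures says: "Primary outcomes include diabetes self-care behaviors, HbA_1c_ level, and diabetes-specific distress". Its next sentence lists the same four behaviors among the secondary outcomes.

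The hypothesis in Design and Setting opens by fixing the time point and the arm, "It is hypothesized that at 3 months postbaseline, the immediate access plus FIT condition", and goes on to predict that this arm "will show the greatest improvements in primary and secondary outcomes compared with the immediate access and the delayed access conditions". It has one time point and two comparators. The only 6-month expectation does not involve FIT: "Results of the immediate access and the delayed access conditions are expected to be similar at 6 months".

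Statistical Analyses makes multiple regressions the primary analysis, "predicting posttreatment and follow-up results from baseline measures and treatment contrasts". The Abstract adds: "Measures are administered at baseline and at 3, 6, and 12 months postbaseline". Sample Size and Retention gives a detectable f² of .046 in these regressions with 210 participants. It states no alpha, power or tested degrees of freedom.

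**The concern.** The article names no lead outcome, no lead contrast and no rule for how many primary outcomes must succeed. If the family of primary tests has no fixed size, its error rate cannot be controlled or even stated. A positive result on one behavior could be reported as a primary finding under the Abstract and as a secondary one under Design and Setting, and that choice could be made after the results are known.

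The sample-size statement adds to this. If f²=.046 belongs to one test on one outcome, the trial was sized as though the question of several primary outcomes did not arise. Any later adjustment would then reduce power below what the article implies.

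**Working it through.** **Inputs from the article.** N=210 and f²=.046 (Sample Size and Retention); three arms, two FIT comparators and a 3-month hypothesis (Design and Setting); two, three or six primary outcomes (Design and Setting, Measures, Abstract).

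**Assumptions, because the article does not state them.** Power 80%; alpha .05 per test unless noted; three equal arms; all 210 participants informative; correlation between outcomes 0 to 0.4.

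**Step 1: reproduce f²=.046.** The test is a noncentral F with noncentrality λ = f²·N, u tested df and v = N−k−1. With baseline plus two contrasts, k=3 and v=206.

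| Test | f² detectable at 80% power | Power at f²=.046 |
|---|---|---|
| 2 df, alpha .05 | .0465 | .795 |
| 1 df, alpha .025 | .0458 | .802 |
| 1 df, alpha .05 | .0377 | .872 |
| 1 df, alpha .0125 | .0539 | .721 |

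The first two rows reproduce the stated figure to within rounding and cannot be told apart without the alpha and power. The first is one unadjusted overall test of the three arms on one outcome. The second is most naturally two contrasts on one outcome; at most it leaves room for two tests in total.

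**Step 2: size of the family at 3 months.** Outcomes × two FIT contrasts gives 2×2=4, 3×2=6 or 6×2=12 tests.

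**Step 3: at least one significant result, no true effect, .05 per test.** For m independent tests the chance is 1−0.95^m: 1−0.95⁴=.185, 1−0.95⁶=.265, 1−0.95¹²=.460. The two contrasts share the FIT arm and outcomes are correlated, so the rates were also simulated.

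| Primary outcomes | Any result, independent tests | Any result, simulated | Any result favoring FIT, simulated | FIT beats both arms on the same outcome, simulated |
|---|---|---|---|---|
| 2 | 18.5% | 17% | 8-9% | 0.9% |
| 3 | 26.5% | 23-26% | 12-14% | 1.3-1.5% |
| 6 | 46.0% | 38-43% | 19-24% | 2.5-2.8% |

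At an outcome correlation of 0.5, the simulated rates for any result fall to 16% for two outcomes and 35% for six.

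**Step 4: other decision rules.** If a 2-df overall test must be significant before the contrasts are examined, the chance is at most 1−0.95²=9.8%, 1−0.95³=14.3% or 1−0.95⁶=26.5%. If FIT must beat both arms, the last column applies when no arm differs. If instead the program works well and FIT adds nothing to it, FIT versus delayed is nearly always significant. Only FIT versus immediate then protects the claim, and for independent outcomes the chance approaches 1−0.975²=4.9% with two outcomes and 1−0.975⁶=14.1% with six.

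**The case against.** The strongest objection is that error control commonly sits in the statistical analysis plan. None is shown, so its absence from a condensed article is no defect. That stands: the accurate wording is that none is stated, and testing each outcome at .05 is an assumption here. It does not cover the contradictory primary list or a sample-size figure that fits one outcome, both of which the article fixes itself.

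A second objection is that superiority over the other two conditions means FIT must beat both, which needs no adjustment across the two contrasts. This is a fair reading and brings the rate under no effect to about 1-3%. The article does not adopt it as a decision rule, however, and it does not remove the multiplicity across outcomes (Step 4).

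A third is that f²=.046 is closest to a 1-df test at .025, so some adjustment may already be included. That is possible. Halving alpha allows for two tests, while the smallest family here has four.

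A reader might also infer that a false-positive primary claim for FIT is likely, because the regressions run at three visits. Pooling six outcomes, two contrasts and three visits gives 1−0.95³⁶=84% for independent tests and about 65-75% in simulation (visit correlation 0.6 assumed). The article does not support that reading. The FIT hypothesis is confined to 3 months, the 6-month expectation is of similarity between two other conditions, and nothing says that one significant result at any visit counts as success. At 3 months no version of the primary list reaches 50%. Secondary outcomes, although included in the hypothesis, cannot inflate a primary claim.

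**Conclusion.** The point holds in limited form. The primary set is multiple, unordered and contradictory, and the stated detectable effect makes no visible allowance for several primary outcomes. With each primary outcome and FIT contrast tested at .05 at 3 months, the chance under no effect of some significant primary result is about 17-19% for two outcomes and 38-46% for six. For a result favoring FIT it is about 8-9% and 19-24%. A rule that FIT must beat both comparators would lower it to about 1-3% under no effect in any arm. These figures rest on the assumed .05 per test, equal arms and outcome correlations of 0 to 0.4. The match of f²=.046 to a single-outcome test rests on an assumed 80% power. The finding is that type I error is undefined and probably inflated; it is not that a false positive is likely.

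**What to change.** 1. Use one primary list in the Abstract, Design and Setting, and Measures. HbA1c and diabetes-specific distress, as in Design and Setting, is the shorter option.
2. Make 3 months, the time point of the stated hypothesis, the only confirmatory one.
3. Name the confirmatory claims: immediate versus delayed access for the program; FIT versus immediate and FIT versus delayed, both required, for the claim that FIT does best.
4. Apply Holm, or a prespecified fixed sequence, across outcomes and claims. With two outcomes and two claims there are four, so Holm's first step is .05/4=.0125. For the FIT claim, enter the larger of its two P values.
5. Report all other outcomes and time points with confidence intervals and no confirmatory claim.
6. Restate the detectable effect with its alpha, power and tested df.

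The change is to wording only. If an analysis plan already contains such a rule, the article should state it or refer to it. The cost is a larger detectable effect: at N=210 and 80% power, 1-df f² is .038 at .05, .046 at .025 and .054 at .0125. Measured from unadjusted testing, the rise under four-way Bonferroni is therefore .038 to .054. A fixed sequence keeps .038 for its first test, but later tests depend on the earlier ones succeeding. Requiring both FIT contrasts also gives the FIT claim less power than either contrast alone.
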